## ***Model selection***

### **Between model selection**

The best performing model for each of the three ML-problems will be used for further analysis of risk factors. To identify the best model for the regression ML-problem we are going to use **Akaike Information Criteria - AIC** as it is applicable to linear models and non-linear models as well and takes into account model performance and its complexity.

For identifying the best performing time-to-event ML-model we will use the **c-index** and the **Brier Score**.

The information criteria scores will be obtained from applying the model to a hold-out/test dataset of the complete dataset.

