### **Inference Analytics**

It is expected that clinical parameters and biomolecule concentrations will interact in complex ways. These multiple interactions are not well captured by classical regression analyses. On the other hand, multiple regression remains the 'gold standard' in the field. To reflect these complexities and demands, we will train four types of models separately for the 1st primary outcome, the 2nd primary outcome, and the primary safety outcome. Those model types include statistical learning (SL), machine learning, and deep learning (DL) approaches. Furthermore, each of the  $3 * 4 = 12$  models will be trained with clinical confounders and with clinical confounders combined with circulating biomolecules. This gives us the ability to eventually compare 24 models and their reflection of interactions between the clinical parameters and biomolecule concentrations.

- A time-to-event machine learning problem to be solved by different candidate models to be compared against each other. These are namely:
- For 1st primary outcome, 1st primary safety outcome and their components
  - Cox regression – SL - classic approach
  - random survival forest – ML – Tree-based ensemble (bagging)
  - gradient boosted model – ML – Tree-based ensemble (boosting)
  - artificial neural network – DL – multi layer perceptron
- A regression ML-problem to be solved by the following candidate models:
- For 2nd co-primary outcome
  - multiple linear regression – SL - classic approach
  - random forest – ML – Tree-based ensemble (bagging)
  - gradient boosted model – ML – Tree-based ensemble (boosting)
  - artificial neural network – DL – multi layer perceptron

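### The risk-factor step takes the single best-scoring model per outcome, yet half the candidates contain no biomolecules, so the marker list can come back empty or rest on one narrowly chosen algorithm

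*SAP*

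**What the plan says.** The section *Inference Analytics* plans four algorithms for each of three outcomes (first co-primary, second co-primary, primary safety), which makes 12 models. Each of these "will be trained with clinical confounders and with clinical confounders combined with circulating biomolecules". The SAP adds: "This gives us the ability to eventually compare 24 models".

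The section *Between model selection* then sets the rule: "The best performing model for each of the three ML-problems will be used for further analysis of risk factors". For the regression problem (nights in hospital) the score is AIC, chosen because it "takes into account model performance and its complexity". For the time-to-event outcomes there are two scores: "For identifying the best performing time-to-event ML-model we will use the" c-index and the Brier score. On the data to be used: "The information criteria scores will be obtained from applying the model to a hold-out/test dataset of the complete dataset". The section *All variables* sets the hold-out at 20%.

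The section *Identification of relevant circulating biomolecules as risk factors* names permutation feature importance as the method, because it can be applied to any type of model. It does not say which fitted model it is applied to, and it asks for no agreement between models.

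**The concern.** The rule uses a prediction contest to decide which model answers an association question. Two things can go wrong.

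- **Empty result.** Permutation importance measures the loss of performance when a variable is shuffled. A variable that is not in the model cannot be ranked. If a clinical-only model is the best scorer for an outcome, this step says nothing about any of the 14 biomolecules for that outcome. That would not mean that the biomolecules are unrelated to the outcome. It would mean that, on one small test set, adding them did not raise a score.
- **Unstable result.** If a combined model wins, the ranking comes from one algorithm. That a method can be applied to any model does not mean that its rankings agree across models. For time-to-event outcomes the SAP names two scores and no rule for when they name different winners, so the choice could be made with the results in view.

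At stake is the only procedure in the SAP that is specified for sorting all 14 biomolecules by relevance to the three main outcomes.

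**Working it through.** **Count of candidates.** The SAP's own figure is reproduced: 3 outcomes × 4 algorithms = 12, and 12 × 2 predictor sets = 24. Reading the three problems as the three outcomes, 24 / 3 = 8 models per outcome, of which 4 (50%) hold clinical variables only.

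**Size of the contest.** The section *Handling errors and missing data* gives 1585 patients. The hold-out is 0.20 × 1585 = 317 and the training set is 1585 − 317 = 1268.

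**Two Cox models on that hold-out.** The SAP gives neither an event rate nor an expected gain from biomolecules, so both are assumed. The simulation used 1268 training and 317 hold-out patients and compared Cox regression on the 19 listed clinical parameters with Cox regression on those 19 plus the 14 biomolecules. Variables were independent. Five clinical variables were prognostic (linear-predictor SD 0.6), as were three biomolecules (SD as in the table). Nominal event rates were 10%, 15%, 20% and 25%, with 300 runs per scenario. The Monte Carlo standard error is at most √(0.5 × 0.5 / 300) = 0.029. Ranges run across the four event rates.

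| Biomolecule SD | Clinical-only scores at least as well | Mean c-index gain on hold-out | SD of that gain |
|---|---|---|---|
| 0 | 72–76% | −0.013 to −0.008 | 0.012–0.022 |
| 0.20 | 41–56% | −0.003 to 0.002 | 0.015–0.026 |
| 0.30 | 25–39% | 0.008 to 0.014 | 0.018–0.029 |
| 0.45 | 5–17% | 0.031 to 0.037 | 0.023–0.033 |

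In the row for SD 0.20, three markers truly affect the outcome, yet the mean gain is about zero because 14 coefficients must be estimated. In the row for SD 0.30, the gain is smaller than its own standard deviation. This compares two models, not the best of eight.

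**Four algorithms, eight candidates.** A smaller simulation (67 runs, 15–16% events assumed, binary outcome as a proxy for survival) used regression, forest, boosting and network. The large-sample AUC for regression was 0.745 clinical and 0.764 combined, a gain of 0.764 − 0.745 = 0.019. A clinical-only candidate won in 19% of runs by c-index (approximate 95% interval 12–30%) and in 12% by Brier score (6–22%). Across this setting and a weaker one (64 runs), the two scores named different winners among the 4 combined models in 44–58% of runs. Top-five biomolecule lists from two algorithms shared 2.6–2.9 of 5 on average.

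**Nights in hospital.** The simulations do not cover the AIC rule. For linear regression, AIC = 2k − 2 log L, so 14 added coefficients raise the penalty by 2 × 14 = 28. The combined model must lower −2 log L by more than 28 to win. A clinical-only winner is therefore possible here too.

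**The case against.** The strongest reply is that the SAP does not stake its aim on this step. The section *Aim of the study* first announces multivariate analyses and brings in machine learning in addition. It also plans an extended multivariate analysis with clinical parameters and biomolecule concentrations. Eight specific hypotheses follow, most of them naming individual markers. None is tied to the best-model rule. A reader might infer that the biomolecule aim can fail outright, or that markers are read only from the winning model. The documents do not support that, and this part of the reply stands. Its reach is limited, however. The multivariate analyses come without a named model or criterion. The hypotheses name only a few of the 14 markers directly, and none tests the full first co-primary composite, nights in hospital or the safety composite.

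A second reply is that the with-and-without contrast may be meant only to show added value, with four algorithms competing. That is plausible: where *Inference Analytics* speaks of candidates, it lists algorithms, and the heading of the importance section presupposes models with biomolecules. But the SAP does not say so, and the plain wording of the rule leaves all eight models eligible.

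A third reply concerns the numbers. In the weaker four-algorithm setting the true gain was almost nil (AUC 0.727 against 0.728). Its clinical-only wins (36% by c-index, 41% by Brier score) therefore do not show that a useful signal was lost. The overlap of 2.6–2.9 of 5 has no same-algorithm baseline, so algorithm dependence cannot be separated from sampling noise. Both criticisms stand.

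Finally, a reader might infer that Cox regression must be the identification model. The SAP argues that classical regression captures interactions poorly and lets algorithms compete on purpose. Imposing Cox would be a trade-off against that rationale, not the correction of an error.

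**Conclusion.** The point holds for the identification step that runs from model selection to permutation importance. As written, the rule can deliver no biomolecule ranking for an outcome, or one that rests on a single algorithm picked on about 317 patients. For time-to-event outcomes it also leaves open which of two scores decides. It does not put the whole aim of the sub-study at risk.

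The count of 4 clinical-only models in 8 follows directly from the SAP. That they are eligible to win is the literal reading, not an explicit statement. The simulated frequencies rest on assumed event rates, effect sizes and independent predictors and are illustrative only. They show that a clinical-only winner is realistic when the gain is modest, and uncommon (5–17% in the Cox comparison) when it is about 0.03 or more. They do not estimate the chance in this dataset.

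**What to change.** Amend the model-selection and importance sections as follows.

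1. Limit the risk-factor step to the models with clinical variables plus biomolecules.
2. Report permutation importance from all four combined models for each outcome. Call a marker robust only if it ranks consistently across them, with the meaning of consistent (rank cut-off and number of models) set before the data are analysed.
3. Report clinical-only against combined performance separately, as the added value of biomolecules.
4. Name one deciding score in advance for the time-to-event outcomes, for example the integrated Brier score, and report the c-index beside it.

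Fixing Cox regression as the sole identification model is optional and not needed to cure the defect.

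The cost is small. All 24 models are already planned, so no new data or models are needed. Importance is reported for 4 × 3 = 12 models instead of 3. The downside is the extra output and possibly a shorter list of markers called robust.

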#### **Aim of the study**

The study aims to identify circulating biomolecules associated with the **severity level of heart disease**. Promising candidate circulating biomolecules were identified using a modified Delphi approach. Details have been published, [7], [8], [9]. For this purpose, different multivariate analyses are performed. In addition, different machine learning (ML) models will be used to predict the **dependent variables**:

- **1st co-primary outcome** – which is a composite of the variables:

- cardiovascular death
- stroke / transient ischemic attack
- hospitalization
  - due to worsening of heart failure or
  - due to acute coronary syndrome

is a time-to-event endpoint consisting of:

- a categorical, nominal scaled variable that can take the two expressions true or false  
and
- the time from admission of the participant in the study till observation of the event.

- **2nd co-primary outcome** – 'nights spend in hospital per year'

is a numeric, discrete scaled variable that ranges from 0 to  $n$  number of nights. We will add one night to each value to enable log transformation in addition to using the collected number of nights spent in hospital.

- **Primary safety outcome** – which is a composite of death, stroke, and serious adverse events of rhythm control therapy.

To increase power and to explore the effect on all events, recurrent events will be analyzed in a separate analysis. In addition, circulating biomolecules predictive of components of the primary outcome will be analyzed. We will also determine biomolecule concentrations associated with the primary safety outcome, its components, and biomolecule concentrations associated with major bleeding (captured as SAE). To determine factors that affect the primary outcome, we plan an extended multivariate analysis including clinical parameters associated with the primary outcome (see Kirchhof et al NEJM 2020, supplementary data and Metzner et al Europace 2021) and biomolecule concentrations.

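### The hospital-nights model is chosen by an AIC scored on hold-out data, with no likelihood or parameter count defined for three of its four candidates

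*SAP*

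**What the plan says.** Under Inference Analytics, the SAP lists four candidates for nights in hospital per year: "multiple linear regression – SL - classic approach", a random forest, a gradient boosted model, and "artificial neural network – DL – multi layer perceptron".

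Under Between model selection, the winner for this regression problem is picked by AIC. The stated reason is that AIC suits the task, "as it is applicable to linear models and non-linear models as well and takes into account model performance and its complexity". The same section then says: "The information criteria scores will be obtained from applying the model to a hold-out/test dataset of the complete dataset". The chosen model goes forward to the risk-factor analysis. The time-to-event problems use the c-index and the Brier score instead.

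Three other places bear on the point. Inside model selection leaves hyper-parameters, and so the size of the network, to a random grid search with cross-validation. All variables sets aside a 20% hold-out to evaluate the final model and plans k-fold cross-validation within the remaining 80%. Aim of the study plans two versions of the outcome: "We will add one night to each value to enable log transformation in addition to using the collected number of nights spent in hospital".

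Nowhere does the SAP state a likelihood, a parameter count or effective degrees of freedom for the forest, the boosted model or the network.

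**The concern.** AIC is minus twice a maximised log-likelihood plus 2k, where k counts the freely estimated parameters. For multiple linear regression both parts are standard. For a bagged forest, a boosted ensemble or a tuned network there is no agreed k, and these models are not usually fitted by maximising a likelihood. The SAP's reason for using AIC, that it carries over to non-linear models, holds for non-linear models fitted by maximum likelihood. It does not by itself cover these three.

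The 2k term also has a specific purpose. It offsets the amount by which a model's fit to its own training data flatters it. On data not used for fitting, that flattery is absent, and over-fitting already shows as larger error. Adding 2k there charges for complexity a second time.

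At stake is which model is used to name the biomolecules linked to a co-primary outcome. The SAP brings in machine learning because it expects interactions that classical regression captures poorly. If the selection rule turns on how parameters are counted, and not on how well nights are predicted, it cannot serve that purpose.

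**Working it through.** The SAP gives no AIC figure to reproduce. The check asks what the rule would do if applied as written.

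**Inputs from the SAP**
- Sample size 1585 (Handling errors and missing data). A 20% hold-out (All variables) is 0.20 × 1585 = 317, leaving 1268 for training.
- 14 biomolecules and, by count of the list, 19 clinical parameters: p = 33.

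**Assumptions, not in the SAP**
- One input column per predictor.
- One hidden layer with h units.
- Every weight and bias counts as a parameter.
- A Gaussian working likelihood.
- The hold-out used for selection is the 20% set.

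**Formulas**
- AIC = n·ln(RSS/n) + 2k
- Linear regression: k = p + 2 = 35
- Network: k = p·h + h + h + 1 + 1 = 35h + 2
- The network wins only if RSS(network)/RSS(linear) < exp(−2(k_network − 35)/n)

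Example, h = 8: k = 282, the extra penalty is 2 × (282 − 35) = 494, and exp(−494/317) = 0.2105. The network must cut the hold-out RSS by 79.0%.

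| Hidden units | k | Extra penalty | RSS cut needed, n = 317 |
|---|---|---|---|
| 1 | 37 | 4 | 1.3% |
| 2 | 72 | 74 | 20.8% |
| 4 | 142 | 214 | 49.1% |
| 8 | 282 | 494 | 79.0% |
| 16 | 562 | 1,054 | 96.4% |
| 32 | 1,122 | 2,174 | 99.9% |

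To put this in terms of R², suppose linear regression reaches 0.10 (an assumption). The network then needs 1 − 0.9 × 0.9875 = 0.11 with one unit, 1 − 0.9 × 0.7918 = 0.29 with two, and 1 − 0.9 × 0.2105 = 0.81 with eight. With 16 units or more, k exceeds the number of hold-out patients.

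For the clinical-only models (p = 19), the required cuts are 13.5% with 2 units, 60.9% with 8 and 98.4% with 32.

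**Forest and boosting.** Here the value of k is open. An illustrative simulation used 10 data sets of 1585 patients with 33 predictors, a strongly non-linear truth and the 80/20 split. Mean hold-out results were:

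| Model | MSE | AIC |
|---|---|---|
| Linear regression (k = 35) | 4.07 | 514 |
| Forest, k = 0 | 3.06 | 353 |
| Same forest, k = number of leaves | 3.06 | 51,889 |
| Boosting, k = number of trees (200) | 3.06 | 753 |
| Same boosting, k = number of leaves | 3.06 | 3,340 |
| Network, 32 units | 1.73 | 2,417 |

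The forest predicts better than linear regression whichever k is used. On these means it wins on AIC only if 353 + 2k < 514, that is, k ≤ 80. The analyst's choice of k settles the ranking. The 32-unit network had lower hold-out error than linear regression in 10 of 10 runs and lower AIC in none. The simulated data show the mechanism only; they do not forecast this trial's results.

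**The case against.** The best defence is that AIC can be extended. With squared-error loss, a Gaussian working likelihood can be written for any predictor, and effective degrees of freedom can be estimated for ensembles and networks. This stands against any claim that AIC is impossible for these models. It does not rescue the rule, because the SAP names no such quantity and the result depends on which one is used. Scoring on the training data would put the penalty where it belongs. The missing k would remain, and a network counted by its weights would still need a 32.3% cut in RSS with 8 units and 82.0% with 32.

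A reader might infer two stronger things that the SAP does not support:
- *That the network always loses and the choice is fixed in advance.* The SAP sets no network size and leaves it to tuning. With one or two hidden units the hurdle is 1.3% or 20.8%, which is attainable. Variable reduction, which the SAP allows, would lower k further.
- *That AIC will be compared between raw nights and log(nights + 1).* Such a comparison would be invalid without a Jacobian term, but no section says it will be made. Selecting separately within each version fits the text equally well. This is an ambiguity, not a demonstrated error.

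The reach is also limited. The rule covers one of three outcome problems, none of the eight specific hypotheses concerns hospital nights, and the step is exploratory. Permutation importance can be run on any of the four models, and the SAP intends to compare them all. That limits the harm, but the model taken forward would still be picked by an undefined rule.

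**Conclusion.** The point holds in this form. The SAP selects the hospital-nights model by an AIC whose k is undefined for the forest, the boosted model and the network, and it adds an in-sample penalty to a hold-out score. The ranking therefore rests on a choice that the SAP does not state and that can decide the winner.

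These two defects follow from the text alone. The numerical size rests on the assumptions listed with the calculation. Under them, networks of about 8 or more hidden units are almost always rejected whatever their accuracy, and networks of one or two units are not. The c-index and Brier score need no parameter count, so the time-to-event selection is untouched. The rule should be replaced before any model is chosen.

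**What to change.** In Between model selection, replace AIC for the regression problem by cross-validated prediction error:
- **Metric:** RMSE as the primary metric and MAE as support.
- **Data:** computed identically for all four model types, in the cross-validation folds of the 80% training set. The 20% hold-out is kept for evaluating the final model, as All variables already provides.
- **Outcome scale:** state whether the raw and log(nights + 1) versions compete. If they do, score both in nights after back-transformation with a retransformation correction such as smearing, because plain back-transformation gives roughly a median and not a mean. If they do not, select within each scale.

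A Poisson or negative binomial deviance might look natural for nights, but it should not be the primary metric. It is undefined for predictions at or below zero, which linear regression on raw nights can produce.

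The cost is SAP wording and slightly more analysis work. No new data are needed, and the folds are already planned.

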## EAST-AFNET circulating biomolecules sub-study

- **Specific hypotheses.** Based on our biomedical knowledge, we developed specific hypotheses that will be tested in the EAST – AFNET 4 biomarker sub-study. These include the following:
  1. BMP10 concentrations are associated with recurrent AF and affect recurrent AF differentially depending on the use of sodium channel blockers (flecainide, propafenone).
  2. FGF23 concentrations are associated with recurrent AF.
  3. A combination of ANG2, FGF23, and BMP10 predicts recurrent AF better than natriuretic peptides.
  4. ESM1 concentrations are associated with stroke (both prior stroke at baseline and future stroke during FU) and with the composite of stroke and cardiovascular death
  5. The ABC bleeding score is associated with major bleeding
  6. The ABC stroke score is associated with stroke and with the composite of stroke and cardiovascular death
  7. BNP is associated with heart failure hospitalizations and with the composite of death or heart failure hospitalization
  8. Angiotensin 2, FGF23 (alone or in combination or in combination with ESM1) are strong predictors for stroke or stroke and ACS, or stroke + ACS + CV death

- The 14 circulating biomolecules:
  - ANG2
  - BMP10
  - Cancer-Antigen 125 (CA-125)
  - Cardiac C-Reactive Protein High Sensitive
  - Creatinine (enzymatic determination)
  - D-Dimer [Explicit units would be "ug FEU/mL]
  - ESM1
  - FBP3
  - FGF23
  - Growth Differentiation Factor-15
  - Interleukin-6
  - IGFBP7
  - NT-proBNP
  - Troponin T high sensitive (cTnT-hs)

all numeric, continuous scaled

To enable evaluation of these circulating biomolecules in context with clinical information, a list of parameters that are associated with the primary outcome will be included in the analysis. A preliminary list will be taken from the existing analyses in the trial. If there are too many candidates, we will do some variable reduction to discard “redundant” variables without using the association with the endpoints to inform that decision (e. g. correlations, PCA, etc.).

See supplement to the main results publication for a list of preselected parameters.

- additional **clinical** parameters collected at baseline:
  - age
    - numeric, discrete scaled
  - gender
    - categorical, nominal scaled – dichotomous
  - random group
    - categorical, nominal scaled – dichotomous
- BMI
  - numeric, continuous scaled
- Heart Failure, determined using heart failure symptoms and LVEF

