### **Inside model selection**

To find the optimal hyper-parameters (not features/variables to use) for each model (except multiple linear - / Cox regression as they do not have hyper-parameters) **Random Grid Search Cross Validation** will be used. As this technique is able to identify near optimal parameters in reasonable time.

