### All variables

A 20 % **hold-out dataset** will be used for evaluating the final model that only relies on the most relevant variables and has been trained on the remaining 80 % of the dataset. At model training time the training set will be further split into **k-fold-cross validation** datasets. The split will be **stratified** for the dependent variable.

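### As written, the SAP's only hold-out set both picks the winning model type and evaluates the final model, so the reported performance is expected to be too high

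*SAP*

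**What the plan says.** Five sections of the SAP bear on this point.

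- **Inference Analytics.** Four model types are trained for each of three outcomes, with and without the biomolecules: "This gives us the ability to eventually compare 24 models".
- **Between model selection.** One winner per problem goes forward: "The best performing model for each of the three ML-problems will be used for further analysis of risk factors". The metrics are AIC for nights in hospital, and c-index and Brier score for the time-to-event outcomes. The section ends with the data source: "The information criteria scores will be obtained from applying the model to a hold-out/test dataset of the complete dataset".
- **Inside model selection.** Cross-validation is assigned to tuning within a model: "To find the optimal hyper-parameters (not features/variables to use) for each model".
- **Data preprocessing, All variables.** A 20% hold-out "will be used for evaluating the final model that only relies on the most relevant variables", with training on the other 80%. The only further division is within the training part: "At model training time the training set will be further split into" k-fold cross-validation sets.
- **Identification of relevant circulating biomolecules as risk factors.** Variables are ranked by permutation importance. The SAP does not say on which data this is computed.

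The SAP mentions no separate validation set, second test set, nested cross-validation or optimism correction.

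**The concern.** A test set gives an unbiased estimate only if nothing about the model was decided on it. If the winner is the candidate that scored highest on the hold-out, part of its lead is chance in those particular patients. Evaluating a final model of that type on the same patients carries the chance component into the reported figure.

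Two things are at stake. The first is how well the final model appears to predict. The second is which model type supplies the permutation importances that name the relevant biomolecules, and identifying such biomolecules is the aim of the sub-study. If permutation importance were also computed on the hold-out, the choice of variables would add further optimism.

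**Working it through.** **Step 1. Reproduce the SAP's count.** 3 outcomes × 4 model types = 12, and × 2 predictor sets = 24, as stated. Selection is within one outcome, so the number competing is 4, or at most 8 if the choice also runs across the two predictor sets.

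**Step 2. Size of the hold-out.** The section Handling errors and missing data gives 1,585 patients. 0.20 × 1,585 = 317 hold-out and 0.80 × 1,585 = 1,268 training. Using the 1,586 of the section Analysis Population gives 317.2, which makes no difference.

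**Step 3. Are the two sets the same?** Between model selection refers to a hold-out or test set without a percentage. All variables defines one hold-out, 20%. Apart from the cross-validation folds inside the training part, no other split is defined. Identity is therefore inferred, but it is the only reading for which the SAP supplies a dataset.

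**Step 4. Precision of a c-index in 317 patients.** The SAP gives no event count. I assume that 10% to 20% of the hold-out have an event (32 to 63) and that the true c is 0.70. The Hanley-McNeil formula for an AUC serves as an approximation, with n₁ events and n₀ non-events:

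SE² = [A(1−A) + (n₁−1)(q₁−A²) + (n₀−1)(q₂−A²)] / (n₁n₀), with q₁ = A/(2−A) = 0.5385 and q₂ = 2A²/(1+A) = 0.5765.

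- 32 events, 285 without: SE = 0.0537.
- 48 events, 269 without: SE = 0.0446.
- 63 events, 254 without: SE = 0.0396.

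**Step 5. Optimism of the selected candidate.** For k equally good candidates whose hold-out errors have correlation ρ:

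optimism = E[max of k standard normals] × SE × √(1−ρ), with E[max] = 1.03 for k = 4 and 1.42 for k = 8.

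The SAP gives no ρ; I take 0.5 to 0.9. For k = 4:

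| Hold-out events | ρ = 0.5 | ρ = 0.8 | ρ = 0.9 |
|---|---|---|---|
| 32 | 0.039 | 0.025 | 0.017 |
| 48 | 0.032 | 0.021 | 0.014 |
| 63 | 0.029 | 0.018 | 0.013 |

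For example, 1.03 × 0.0537 × √0.5 = 0.039. For k = 8 the range is 0.018 to 0.054.

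**Step 6. Candidates that truly differ (simulation, k = 4, same SE and ρ ranges).** With true c of 0.70, 0.69, 0.68 and 0.67, the optimism is 0.008 to 0.037. With 0.72, 0.70, 0.68 and 0.66, it is 0.004 to 0.032. It is upward in every scenario.

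**Step 7. After the fix.** If the 317 patients play no part in selection, the expected selection optimism is zero. The hold-out SE stays at about 0.040 to 0.054.

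**The case against.** The strongest defence is that the SAP never states that the two hold-outs are one set. It also does not expressly confine the k-fold splits to tuning, so a separate selection step could have been intended. That stands as a qualification. It does not rescue the text, because a selection set that was intended but not defined also has to be written in.

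Three narrower objections:

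- *The sentence on data source speaks of information criteria, which literally fits only AIC.* It closes a section covering all three metrics, and no other source is given for the c-index or Brier score. Even read narrowly, the model for nights in hospital would still be chosen on the hold-out.
- *The final model is a reduced version of the winner.* Its type was still chosen on those patients' outcomes. The figures above are for the winner's own score; the reduced model inherits the optimism to the extent that its errors follow the winner's.
- *The bias is modest.* For four candidates it is at most 1.03 × √0.5 = 0.73 of one SE under these assumptions, and no treatment-effect test in the SAP depends on it. This stands and limits the weight of the point, but not its direction.

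A reader might also infer three stronger points that the SAP does not support.

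- *That the choice of clinical predictors contradicts the SAP's own outcome-blind rule.* On those predictors the SAP says "A preliminary list will be taken from the existing analyses in the trial". The rule against using endpoint associations governs only the later removal of redundant variables, so the two statements are compatible.
- *That one winner is drawn from 24 models.* There is one winner per outcome, from four to eight candidates.
- *That the apparent gain from biomolecules is biased in a known direction.* Clinical variables enter both predictor sets. If the best model is taken within each set, both scores are inflated and part of the bias may cancel. The calculation above does not address the difference.

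**Conclusion.** The point holds. Followed as written, the plan lets the same 317 patients select the model type and evaluate the final model, and the reported performance is then expected to be too high. This rests on reading the two hold-outs as one set, which is an inference, though the SAP defines no alternative.

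The size is uncertain because the event count, the true c-index and the between-model correlation are all assumed. For four equally good candidates the c-index optimism is about 0.013 to 0.039. It falls to as little as 0.004 when the models truly differ, and reaches 0.054 only if eight equally good candidates compete. No size was calculated for the Brier score or for the AIC-based choice for nights in hospital. No conclusion is drawn about the direction of any bias in the biomolecule gain.

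**What to change.** State in the SAP which data select and which data evaluate:

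1. Choose the model type and the relevant variables by repeated or nested cross-validation within the 80% training set (1,268 patients). Carry out imputation, scaling, tuning and permutation importance inside the folds.
2. For each outcome, lock the final clinical-only model and the final clinical-plus-biomolecule model before the hold-out is opened.
3. Use the 20% hold-out (317 patients) once. Report the performance of both locked models and their difference with a bootstrap 95% confidence interval.

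If a separate validation set was intended for choosing between models, define it and its size instead.

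The cost is SAP wording, some computing time and a slightly lower stated performance. No additional patients or data are needed. The change should be made before analysis, because a hold-out that has been used for selection cannot be made independent again.
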